### Strategies to ensure implementation of the intervention and avoid loss to follow-up

For the project to be successful, we will need to maintain our collaborations with the schools for at least four years. Therefore, all activities associated with the project must conform to the needs and interests of each school. Specific activities will be designed to promote continuity, including visits by the research team and periodic mailings to each school informing them of the progress of the study and recognizing their crucial role. The importance of the control group in the study will also be emphasized.

The final follow-up evaluation will occur six years after inclusion, when the participants will have left the participating school. At least three telephone contact numbers and the addresses of parents and tutors will be obtained early in the study. If a student is not easily located for the final evaluation, additional efforts will be made to contact them by telephone and letter. Efforts will be made to minimize the rate of loss to follow-up to reduce any possible bias resulting from loss to follow-up and to adequately assess the impact of the intervention.

#### **
*Outcome assessments*
**

The measures, variables, and timeline are summarized in Table 1. The baseline prevalence of smoking in each school will be assessed by an external evaluator who will be blinded to the group (intervention or control) to which the school has been allocated. All outcome assessors and data analysts will also be blinded to school allocation. To evaluate the effectiveness of blinding, these individuals will be asked to choose the arm to which they believe each school was assigned (possible answers: intervention, control, or unknown). Individuals who respond “intervention” or “control group” will be asked to indicate what led to the formation of that belief. The primary outcome measure will be the prevalence of smoking at years three and six from enrollment. This will be assessed by self reports of tobacco consumption, where smokers are defined as those who consume more than one cigarette per week.

#### **
*Statistical analysis*
**

##### 

**Sample size** A recent study on smoking in adolescents aged 14-15 years (third year of ESO) found that the prevalence of regular tobacco use in the Balearic Islands was 14% [13]. Using this as the prevalence for our control group and presuming that our intervention will reduce the prevalence of tobacco consumption in the intervention group by at least 40%, the use of 1,002 students per group will yield a statistical power > 80% for our between-group comparisons, assuming a bilateral α error of 5% and a 10% loss of participants to follow-up. The cluster size will be approximately 100 adolescents per municipality; we expect a 0.02 intra-class correlation coefficient [14], yielding a 2.98 cluster design effect. The design effect was calculated using the formula: Deff = 1 + (m – 1) * ICC; where “Deff” corresponds to the design effect, “m” is the cluster size and “ICC” is the intraclass correlation coefficient. The target sample size for each group was calculated to be 1,113 students, or 2,226 students in total. To achieve this sample size, students in the first year of ESO (aged 12-13 years) will be recruited over two consecutive years at 22 schools in the Balearic Islands.

##### 

**Analytic strategy** We will test for significant differences in baseline characteristics between the control and intervention groups. We will perform a descriptive and cluster analysis with continuous variables summarized using means and standard deviations for normal distributions, and by medians and 25^th^ and 75^th^ percentiles for non-normal distributions. All data analyses will involve intention-to-treat populations (i.e., all randomized patients, regardless of participation in any treatment session). This approach will reduce the bias that may occur when participants that fail to receive the assigned treatments are excluded from the analysis. All tests will be two-sided, and α-values of 0.05 will be considered statistically significant.

We will compare the smoking prevalence of adolescents in each group at 12 months against the usual null hypothesis of no difference between groups. We will use the Chi-squared test, taking into account the “variance inflation factor” of the adolescent cluster and intraclass correlation coefficient. We will also calculate 95% confidence intervals to assess the clinical significance of our intervention. In our multivariate analysis, we will adjust for potential confounders, if any, using a multilevel logistic regression model. We will estimate the relative and absolute risk reductions and the number needed to treat (i.e., the estimated number of adolescents who must be treated with our intervention rather than the existing school interventions for one additional adolescent to be prevented from smoking), which will be calculated as the reciprocal of the difference between the prevalence of adolescent smokers in the intervention and control groups. All estimates will include 95% confidence intervals.

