**Methods/Design:**

The proposed multi-center, cluster-randomized controlled trial will be stratified by the baseline prevalence of smoking in schools. Municipalities with fewer than 100,000 inhabitants will be randomly assigned to a control or intervention group. One secondary school will be randomly selected from each municipality. These schools will be randomized to two groups: the students of one will receive any existing educational course regarding smoking, while those of the other school will receive a four-year, class-based curriculum intervention (22 classroom lessons) aimed at reinforcing a smoke-free school policy and encouraging smoking cessation in parents, pupils, and teachers. The intervention will also include annual meetings with parents and efforts to empower adolescents to change the smoking-related attitudes and behaviors in their homes, classrooms and communities.

We will enroll children aged 12-13 years as they enter secondary school during two consecutive school years (to obtain sufficient enrolled subjects). We will follow them for five years, until two years after they leave secondary school. All external evaluators and analysts will be blinded to school allocation.

The aim of this study is to analyze the effectiveness of a complex intervention in reducing the prevalence of smoking in the third year of compulsory secondary education (ESO) and two years after secondary school, when the participants are 14-15 and 17-18 years old, respectively.

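### The primary outcome has two unranked time points and no success rule; if either one suffices, testing each at two-sided 0.05 takes the overall error above 5%

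*Protocol article*

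**What the plan says.** Outcome assessments gives one primary measure at two times: "The primary outcome measure will be the prevalence of smoking at years three and six from enrollment". The abstract (Methods/Design) puts the same pair into the aim, namely "reducing the prevalence of smoking in the third year of compulsory secondary education (ESO) and two years after secondary school", and ranks neither first.

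The Analytic strategy sets the significance rule: "All tests will be two-sided, and α-values of 0.05 will be considered statistically significant". The Sample size paragraph uses the same undivided level, "assuming a bilateral α error of 5% and a 10% loss of participants to follow-up", and claims that "the use of 1,002 students per group will yield a statistical power > 80% for our between-group comparisons". Its control prevalence, 14%, is the figure for ages 14-15 (third year of ESO). No prevalence is given for ages 17-18.

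The protocol gives no testing order, no division of the 5%, and no statement that both time points must succeed or that one is enough.

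Two other places disagree on timing. The only between-group comparison with a stated time, in the Analytic strategy, is at 12 months. Table 1 schedules the smoking prevalence form once the fourth ESO year is over and again two years past graduation, so it lists no year-three assessment.

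**The concern.** With two primary time points of equal standing and 0.05 for every test, a reader of the final report cannot tell which result decides the trial. If a significant difference at either time counts as a positive trial, the intervention has two chances at the full 5% and the declared error rate does not describe the primary conclusion. If both are required, there is no inflation, but the power claim, built on one time point, does not describe the chance of success. Either way, the rule has to be fixed before the data are seen.

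**Working it through.** **Inputs from the protocol.** Two primary time points (Outcome assessments); two-sided 0.05 for every test (Analytic strategy); 14% in controls, a 40% relative reduction (14% to 8.4%), 1,002 per group, 10% loss, cluster size 100, ICC 0.02 (Sample size). **Assumed:** either time point suffices for success, and the correlation ρ between the two test statistics lies between 0 and 0.9. The protocol gives neither.

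**1. Error rate if either time point suffices.**
- Upper bound for any correlation: 0.05 + 0.05 = 10%.
- Independent tests: 1 − (1 − 0.05)² = 1 − 0.9025 = 9.75%.
- Correlated tests: 1 − P(|Z₁| < 1.96 and |Z₂| < 1.96), with Z₁, Z₂ bivariate normal.
- Favourable direction only: 1 − P(Z₁ < 1.96 and Z₂ < 1.96), where positive Z favours the intervention.

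| ρ (assumed) | Any false significant result | False claim of benefit |
|---|---|---|
| 0 | 9.75% | 4.94% |
| 0.5 | 9.07% | 4.54% |
| 0.7 | 8.35% | 4.17% |
| 0.9 | 7.04% | 3.52% |
| One test only | 5% | 2.5% |

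**2. The plan's own sample size, needed for the cost of any fix.**
- Design effect: 1 + (100 − 1) × 0.02 = 2.98. This reproduces.
- Allowance for loss: 1,002 / 0.9 = 1,113. This reproduces.
- Students per group for 80% power without clustering (14% v 8.4%, pooled variance, two-sided 0.05): mean prevalence 0.112; n = [1.96 × √(2 × 0.112 × 0.888) + 0.8416 × √(0.14 × 0.86 + 0.084 × 0.916)]² / 0.056², which rounds up to 497.
- With clustering: 497 × 2.98 = 1,481, not 1,002. The stated 1,002 does not reproduce. A design effect of 1.98 comes close (497 × 1.98 = 984), but that is not the one stated.
- Power at 1,002 per group with 2.98: effective n = 1,002 / 2.98 = 336.2; power = Φ[(0.056 × √336.2 − 1.96 × 0.4460) / 0.4442] = Φ(0.344) ≈ 63%. With 1.98 it is about 81%.

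The sample size discrepancy is a separate problem. It does not affect step 1, but it determines how costly each remedy is.

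**3. Candidate success rules.**
- Fixed order, year three then year six, each at 0.05: overall error at most 5%, because year six can be claimed only after year three is significant. No added students for the first test. At 63% power the first test fails in 1 − 0.63 ≈ 37% of trials with the assumed effect (about 19% at 81% power).
- Split, 0.025 each: overall error at most 5% (4.94% if independent). The unclustered n rises from 497 to 602; 602 × 2.98 = 1,794 per group, or 1,994 with 10% loss. Power at 1,002 per group falls to about 52%.
- Both required at 0.05: error at most 5%, but power for success cannot exceed that of the weaker time point.

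**The case against.** The strongest reply is that the protocol never says one time point is enough. It speaks of a single primary outcome measure and joins the two times with a conjunction; if both must succeed, the error is at most 5%. The 0.05 line can be read as a general convention, and an analysis plan that is not shown might order the tests. This stands in part. A reader might infer that the trial will claim success on either time point and so runs a 10% error; the protocol does not say that, and the figures above are conditional on it. But the point is not only silence. The protocol fixes two unranked primary times and 0.05 for all tests, and an analysis plan that ordered or split them would have to replace that line.

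Three further cautions stand. First, it is tempting to read 10% as the chance of falsely claiming benefit. It counts errors in both directions, and positive correlation is likely because the same students are measured twice. Second, that year three and year six are each tested is itself inferred from the outcome definition and the all-tests rule, since the analysis text names only 12 months. Third, a reader might suppose that year-three results will be unveiled years before year six and steer what follows. No separate reporting or interim analysis is described, and analysts are to be blinded to allocation.

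Finally, gating year six on year three subordinates the long-term question, although the abstract's Discussion motivates the trial by the lack of long-term effects in earlier interventions. That is a real cost of the proposed fix.

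**Conclusion.** The concern holds conditionally. The protocol sets two unranked primary time points, applies an undivided 5% to each test, and sizes the trial on one of them. If significance at either counts as success, the family-wise error is 7.0% to 9.75% for correlations of 0.9 to 0, and at most 10%; false claims of benefit are about 3.5% to 4.9% instead of 2.5%. Even at correlation 0.9 the declared 5% is exceeded. If both are required there is no inflation. The protocol supports neither reading over the other, so the defect is the missing success rule, made worse by conflicting assessment and test times. It should be corrected, but it does not show that the trial will run at a 10% error.

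**What to change.** First reconcile the times: years three and six in Outcome assessments, 12 months in the Analytic strategy, and the two post-fourth-year times in Table 1. The abstract's five-year follow-up also needs to agree with the six years given elsewhere. A year-three test cannot be the gate until the schedule contains a year-three assessment.

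Then state the success rule: the year-three comparison, on which the sample size is built, is tested first at two-sided 0.05; year six is tested confirmatorily at two-sided 0.05 only if year three is significant, and is otherwise reported as an estimate with its 95% interval.

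This needs no extra students for the first test and a short edit once the times agree. The downside is that year six is supportive only whenever year three fails: roughly 37% of trials with the assumed effect, at 1,002 per group and a design effect of 2.98. If the sponsor regards the long-term result as decisive, requiring both time points or splitting the 5% also controls the error, at the costs shown above. The choice should be written down with its reason.

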### Limitations

One of the main limitations of community studies is the possibility of contamination, such as would occur if teachers from neighboring schools met and compared notes regarding the intervention and/or control programs. To avoid this type of contamination, the randomization unit will be the municipality. Another possible limitation is that the intervention will be carried out among students who attend the same school. This could reduce the variability among study subjects; however, we will solve this by using a sufficiently large sample. There may also be a selection bias, with higher rates of non-participation by students attending the intervention schools compared to the control schools. However, in our pilot study implementing the intervention, the response rate to the first evaluation survey of tobacco use in 14 year olds was 85%.

Long-term follow-up of former students can be difficult because many youths move away from home and have life experiences that complicate follow-up. This may result in selection biases that could compromise the internal validity of the study. Consequently, efforts will be made to collect as many contact details as possible before students leave the school (e.g., the physical addresses of their parents, telephone numbers, e-mail addresses, and social network information). Multiple efforts will be made to maintain contact with former students and their families, thus minimizing the rate of loss to follow-up.

To guarantee the comparability of the control and intervention groups, the municipalities will be stratified according to the baseline prevalence of smoking in the school prior to the intervention.

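### On the plan's own inputs, 1,002 analysed pupils per group give about 63–66% power for the year-three comparison, not more than 80%

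*Protocol article*

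**What the plan says.** All of the inputs stand in one paragraph, Sample size, under Statistical analysis in the protocol article.

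- Control prevalence: a survey of pupils aged 14–15 (third year of ESO) found that "the prevalence of regular tobacco use in the Balearic Islands was 14" per cent.
- Effect: "presuming that our intervention will reduce the prevalence of tobacco consumption in the intervention group by at least 40" per cent.
- Error rate and loss: "assuming a bilateral α error of 5% and a 10% loss of participants to follow-up".
- Clustering: "The cluster size will be approximately 100 adolescents per municipality", and "we expect a 0.02 intra-class correlation coefficient [14], yielding a 2.98 cluster design effect". The formula given is 1 + (m – 1) × ICC.
- Result: "the use of 1,002 students per group will yield a statistical power > 80% for our between-group comparisons".
- Enrolment target: 1,113 per group, 2,226 in total, at 22 schools.

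The Analytic strategy paragraph plans a chi-squared test that allows for the variance inflation due to clustering. The power calculation should therefore carry the same inflation.

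**The concern.** The paragraph gives the inputs, the design-effect formula and the answer, and the answer does not follow from the inputs. A comparison of 14% with 8.4% needs close to 500 pupils per group before any allowance for clustering. A design effect of almost 3 takes that to nearly 1,500, yet the plan stops at 1,002.

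At stake is how a null year-three result would be read. Under the stated power, the chance of missing a true 40% reduction is below one in five. Under the plan's own assumptions it is 34–37%. Readers would treat a non-significant result as stronger evidence against the intervention than the design can supply.

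**Working it through.** **Inputs**, all from the Sample size paragraph: p1 = 0.14; p2 = 0.14 × (1 – 0.40) = 0.084; difference 0.056; mean 0.112; two-sided α = 0.05 (z = 1.960); 80% power (z = 0.8416); m = 100; ICC = 0.02; loss 10%; 22 schools, so 11 per arm if split equally.

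**Step 1: figures that reproduce.**
- Design effect: 1 + 99 × 0.02 = 2.98, as stated.
- Enrolment: 1,002/0.9 = 1,113, as stated. So 1,002 is the analysed number and loss is the only step between the two. The design effect cannot have been applied later.
- Cluster size: 2,226/22 = 101 per school, which agrees with about 100. The 100 is therefore the total over both recruitment years, not one year's intake.

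**Step 2: sample size for 80% power.** Pooled two-proportion formula:

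n = [1.960 × √(2 × 0.112 × 0.888) + 0.8416 × √(0.14 × 0.86 + 0.084 × 0.916)]² / 0.056²

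= [0.8741 + 0.3739]² / 0.003136 = 496.7 per group without clustering.

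- With the design effect: 496.7 × 2.98 = 1,480 analysed per group.
- With 10% loss: 1,480/0.9 = about 1,645 enrolled per group.
- Shortfall: 1,480 – 1,002 = 478 analysed, or 1,645 – 1,113 = 532 enrolled, per group.

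**Step 3: power at the stated size.** Effective n = 1,002/2.98 = 336.2 per group.

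z = [0.056 × √336.2 – 0.8741] / 0.4442 = (1.0269 – 0.8741)/0.4442 = 0.344, so power = 63.5%.

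**Step 4: smaller clusters after loss.** 1,002/11 = 91.1 analysed per school. Design effect = 1 + 90.1 × 0.02 = 2.80; effective n = 1,002/2.802 = 357.6; z = 0.416; power = 66.1%.

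**Step 5: other ways to reach the stated figure.** The analysed number is 1,002 and the design effect 2.98 unless noted.

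| Variant | Power |
|---|---|
| Unpooled variance | 63.7% |
| Arcsine | 64.1% |
| Continuity correction | 58.8% |
| All 1,113 analysed, no loss | 68.0% |
| One-sided 5% (contradicts the plan) | 74.5% |
| One-sided 5%, all 1,113 analysed | 78.4% |
| No design effect | 97.8% |

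No variant that keeps the design effect of 2.98 reaches 80%.

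**Step 6: detectable effect.** Solving for 80% power with 1,002 analysed per group gives a relative reduction of about 48% at a design effect of 2.98 (14% versus 7.3%), and about 46% at 2.80 (14% versus 7.5%).

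**The case against.** The core arithmetic has no good answer. The phrase about a reduction of at least 40% does not help, because 40% is the design value and 46–48% would be needed. The objections that carry weight concern how far the point reaches.

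- **Cause of the error.** A reader might infer that an ICC of about 0.01 was used, since 1,002/497 is about 2.0. The document does not support this. 2 × 497 = 994 is not 1,002, whereas 336 × 2.98 = 1,001.3 rounds up to 1,002, which would place the fault in the unclustered number instead. Neither route is documented.
- **Attrition.** A reader might set the 10% loss against the pilot, where "the response rate to the first evaluation survey of tobacco use in 14 year olds was 85" per cent. That is a survey response rate from a single pilot school, cited in Limitations in answer to a concern about non-participation. It is not attrition from a consented cohort, and it does not show that 10% is wrong.
- **Limitations wording.** On pupils sharing a school, the article says: "This could reduce the variability among study subjects; however, we will solve this by using a sufficiently large sample". It is tempting to read this as a mistaken claim that more pupils per school cure clustering. The sentence does not say where the extra pupils would come from, and a larger sample may equally mean more schools.
- **Year six.** The primary outcome is prevalence at years three and six, but the 14% belongs to ages 14–15. The Discussion gives 21% regular smoking at age 16 in the European Union. If control prevalence at year six were 21% (an assumption), a 40% reduction to 12.6% with effective n 336 would have about 83% power. The shortfall cannot be asserted for the whole trial. This objection stands and limits the point to year three.
- **Stratification.** Stratifying by baseline school prevalence may remove some between-school variance. The document gives no figure and claims no gain in the power calculation, so this does not rescue the statement. The corrected figure should still be labelled as unstratified.
- **Lower figures.** Unequal school sizes or a small-sample t reference could push power lower. The article gives no spread of school sizes, and a t reference is not the planned test, so neither belongs in the correction.

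**Conclusion.** The point holds for the year-three comparison. The claimed power above 80% is wrong on the plan's own inputs: it is about 63% at the stated design effect of 2.98, and about 66% if the design effect uses about 91 analysed pupils per school. The type II error for the planned effect is therefore 34–37%, not under 20%.

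The result assumes 14% control prevalence, an ICC of 0.02, equal cluster sizes, 11 schools per arm, 10% loss, a normal approximation and no gain from stratification. Equal cluster sizes, the equal split of schools, the approximation and the absence of a stratification gain are working assumptions; the rest is stated in the article. The conclusion concerns the stated power. It does not establish where 1,002 came from, that the loss allowance is wrong, or that the year-six comparison is underpowered.

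**What to change.** Replace the power sentence in the Sample size paragraph with wording such as: with 1,002 analysed pupils per group (1,113 enrolled), about 100 pupils per school and an ICC of 0.02, power to detect 14% versus 8.4% at year three is about 63%, or about 66% allowing for smaller clusters after loss, ignoring stratification; 80% power is reached for a relative reduction of about 46–48%. Add that 80% power for a 40% reduction would need about 1,480 analysed, or about 1,645 enrolled, per group. Stating only the detectable reduction would also serve.

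If the sponsor has a calculation behind 1,002 that uses inputs other than those printed, those inputs should be given and the paragraph reconciled with them.

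The cost is a change of wording and a less favourable published figure. Correcting the statement requires no additional schools or pupils and no change to the analysis.

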### Study population

The populations of the included municipalities vary from 11,000 and 30,000 inhabitants. The main economic activities of these communities are tourism and farming.

The study participants will consist of all 12-13 year-old students, who enrolled in the first grade of compulsory secondary education (ESO) over two consecutive academic periods (i.e., 2011-12 and 2012-13). The intervention will take place over the four years during which these adolescents are enrolled in ESO. Written informed consent will be obtained from all students and from at least one parent/guardian per student, according to the declaration of Helsinki.

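### The 2.98 design effect assumes schools of equal size, which the enrolment rule does not provide; whether it is too small depends on a spread in school size that the protocol does not give

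*Protocol article*

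**What the plan says.** Protocol article, Statistical analysis, Sample size: "The cluster size will be approximately 100 adolescents per municipality". With an expected ICC of 0.02 this is put into 1 + (m − 1) × ICC, "yielding a 2.98 cluster design effect". It is the only inflation formula printed, and it has no term for variation in m. The section claims that "the use of 1,002 students per group will yield a statistical power > 80" per cent, "assuming a bilateral α error of 5% and a 10% loss of participants to follow-up", and sets a target of 1,113 per group from 22 schools.

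Study population: the participants are "all 12-13 year-old students, who enrolled in the first grade of compulsory secondary education (ESO) over two consecutive academic periods", subject to written consent. No maximum per school is stated. On the towns: "The populations of the included municipalities vary from 11,000 and 30,000 inhabitants".

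Inclusion criteria: where a municipality has several secondary schools, one is drawn at random.

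Random assignment: the only stratification factor is baseline smoking prevalence, so nothing balances school size between the arms.

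Analytic strategy: the group comparison is a chi-squared test that allows for a variance inflation factor and the ICC. The factor's formula and value are not stated. A multilevel logistic model is named for the adjusted analysis.

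**The concern.** The single-m formula describes a trial with equal clusters. This trial takes whatever intake each school has, so its clusters will not be equal. At a fixed mean size and ICC, any spread in size raises the variance of a comparison of pooled pupil proportions, because large schools contribute more than in proportion to their size. A design effect that leaves this out makes the planned power look better than it is.

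The same matter arises in the analysis. If the inflation factor in the chi-squared test were computed from the mean school size, the variance of the arm difference would be understated and the test would reject too often under the null, even with the ICC known.

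**Working it through.** **Inputs from the protocol.** Control prevalence 14%; 40% relative reduction, so 8.4% in the intervention group; two-sided 5%; 1,002 analysed per group; 10% loss; ICC 0.02; m about 100; 22 schools; town populations 11,000 to 30,000.

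**Assumptions.** Eleven schools per arm. School intake proportional to town population, with towns either spread evenly over the range or half at each end.

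**The plan's own figures.** 1 + (100 − 1) × 0.02 = 2.98, which reproduces. 1,002 / 0.9 = 1,113, which reproduces. The 1,002 does not: 14% against 8.4% needs 497 per arm for 80% power before clustering, and 497 × 2.98 = 1,481.

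**School size after loss.** 2 × 1,002 / 22 = 91.1 analysed per school. With equal schools, 1 + (91.1 − 1) × 0.02 = 2.80.

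**CV under the assumption.** The midpoint of the range is 20,500.
- Even spread: (19,000 / √12) / 20,500 = 0.27, CV² = 0.0716.
- Half at each end: 9,500 / 20,500 = 0.46, CV² = 0.2148.

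**Design effect with unequal sizes:** 1 + [(1 + CV²) × mean m − 1] × ICC.
- Mean 100, even spread: 1 + (107.16 − 1) × 0.02 = 3.12.
- Mean 100, half at each end: 1 + (121.48 − 1) × 0.02 = 3.41.
- Mean 91.1, even spread: 1 + (97.61 − 1) × 0.02 = 2.93.
- Mean 91.1, half at each end: 1 + (110.65 − 1) × 0.02 = 3.19.

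**Break-even after loss.** The factor equals 2.98 when (1 + CV²) × 91.1 = 100, so CV = √(100 / 91.1 − 1) = 0.31.

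**Power at 1,002 per group.** The effective n is 1,002 / Deff, and z = [0.056 × √n − 1.96 × √(2 × 0.112 × 0.888)] / √(0.14 × 0.86 + 0.084 × 0.916). At 2.98, n = 336 and z = 0.344, so power is about 63%.

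| Mean m | Size spread | Deff | Power |
|---|---|---|---|
| 100 | equal | 2.98 | 63% |
| 100 | even spread | 3.12 | 61% |
| 100 | half at each end | 3.41 | 58% |
| 91.1 | equal | 2.80 | 66% |
| 91.1 | even spread | 2.93 | 64% |
| 91.1 | half at each end | 3.19 | 60% |

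**The test, if the mean-size formula were used.** The large-sample approximation is 2 × [1 − Φ(1.96 × √(2.80 / Deff))], which gives about 5.5% at 2.93 and 6.6% at 3.19. Simulation (beta-binomial counts, prevalence 14%, ICC held at 0.02, 22 schools, mean 91 analysed, critical value 3.841, 40,000 runs per scenario) gives about 4.9% with equal schools, 5.3% with the even spread and 6.4% with half at each end. Repeat runs, and different ways of drawing the even spread, moved these by up to about 0.4 points. With the size-weighted factor the test stays at about 5% in both unequal scenarios. With the fixed value 2.98 in place of a mean-size factor, the approximation gives 4.8% and 5.8%.

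**The case against.** Four arguments stand on the other side.

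First, a reader might infer that the test itself understates clustering. The protocol does not show this. The sample size section gives its formula as the way the planning figure was obtained, and the analytic strategy does not say that the test uses that formula, the value 2.98 or a mean school size. Cluster-adjusted chi-squared tests can use the actual cluster sizes, and an analysis plan not shown may say so. The figures of 5.3% to 6.4% are therefore conditional.

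Second, a reader might infer that 2.98 is certainly too small. It is too small at a mean of 100 for any CV above zero. But 2.98 was computed before loss, and at 91 per school it exceeds the equal-size value of 2.80 by about 6%. Under the even spread the design effect is 2.93, still below 2.98. The protocol does not present this margin as an allowance for unequal sizes, and the margin runs out at a CV of about 0.31, inside the assumed range.

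Third, town population is a weak guide to school size. One school is drawn per town, larger towns may have several, and consent also affects intake. The CV range is an assumption, not the plan's own figure.

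Fourth, the effect is modest. Moving the ICC from 0.020 to 0.0215 gives 1 + 99 × 0.0215 = 3.13, about the same shift as a CV of 0.27.

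None of this makes the equal-size formula fit a design that takes each school's intake as it comes.

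**Conclusion.** The point holds as a modest planning correction. The 2.98 is computed correctly from its formula, but the formula is exact only for equal schools and the enrolment rule does not provide them. With intake proportional to town population, an unequal-size design effect would be 5% to 14% above 2.98 at 100 per school. At 91 per school it would lie between slightly below 2.98 and 7% above it (3.19 / 2.98 = 1.07). Power at 1,002 per group would be 2 to 5 points lower than at 2.98 in the first case, and between about 1 point higher and 3 points lower in the second.

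This is small beside the gap between the claimed power of more than 80% and the roughly 63% that 1,002 per group gives at the plan's own 2.98. That gap is a separate matter, but it leaves no slack to absorb the size term. An excess type I error is not shown; it is a risk only if the factor left open in the analytic strategy is filled with the mean-size formula. The results rest on an ICC of 0.02, 22 schools split equally between the arms and the assumed CV range.

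**What to change.** 1. In the sample size section, replace the single-m formula with 1 + [(1 + CV²) × mean m − 1] × ICC. Take the CV and mean from the enrolment figures of the selected schools, and state whether the mean is before or after loss. If those figures are not yet available, give a range of CV.
2. Restate the power from the recomputed design effect in the same revision that corrects the claim of more than 80%.
3. In the analytic strategy, name the inflation factor for the chi-squared test. The arm-specific size-weighted form, 1 + (Σ m_j² / Σ m_j − 1) × ICC with m_j the number analysed in school j, uses data the trial will hold anyway.

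The cost is one formula in each section and a lower stated power. The recalculation needs no extra pupils or data beyond school enrolment. How to respond to the power shortfall itself is a separate decision.
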